#### Programme-related costs

We use a step-down costing methodology^39^ whereby costs from programme accounts are entered into a customised tool created in MS Excel. Cost data are entered regularly into the tool, which is adapted each year to reflect the changing cost structure of the trial at different phases of activity. Using a step-down method, the main worksheets for entering data allocate costs to one of the following categories: staff, material, capital and joint costs. Costs are also divided into start-up and implementation costs, and between intervention, monitoring and evaluation and research costs. As these data are financial or accounting costs, they are converted to economic costs. This means that capital costs are annualised over their expected useful life, and any donated goods or volunteer time appearing as a zero costs in accounting data—or not appearing in the accounting data in any form—will be added to the cost sheets and assigned their current market value.^40–42^ Key informant interviews with project leads assist in identifying any donated goods requiring revaluation and in allocating joint costs between programme components. The allocation of joint costs to programme components and activities is also informed by monthly staff time sheets.

Summary Excel worksheets present the costs by programme component such as women's groups or health service strengthening. A single summary worksheet also summarises the total cost data, allows effect data to be entered and calculates the cost-effectiveness results.

### Provider or health system costs

Provider costs or costs to the health system will be calculated for MTCs, Primary Health Centres, community workers and VHSNCs.

#### Malnutrition treatment centres and primary health centres

MTCs provide care for SAM. Demand for these services may increase if SAM is better identified in the community and/or systems for referring children to MTCs are improved. Conversely, demand for these services may decrease if SAM is prevented by improved early child nutrition.

We will estimate any change in the demand for MTC services resulting from the intervention, and the concomitant value of any additional care provided. The trial's routine monitoring forms will capture the number of children admitted for SAM at MTCs. Differences in admissions between intervention and control areas will be attributed to the trial activities. Primary data on the average unit cost of care for SAM will be collected from the two MTCs in the project area. A simple cost-capture form was developed for facility data collection after an introductory meeting with centre managers. Data from the cost-capture form will be used to complement existing data from centre reports, patients’ records and published national and state reports relating to MTCs. Costs of services provided by the MTCs will be calculated using a step-down approach.^39^

For Primary Health Centres, any change in demand for primary care will be identified in the trial's routine monitoring forms as described above. Any cost of that change in demand will be calculated using published data on the unit costs of treatment at Primary Health Centres.^43^

#### Community workers

The CARING intervention may increase the workload of community health workers by increasing demand for their services. Conversely, the new community-based worker (or SPK) introduced by the CARING trial, together with a stronger emphasis on preventive activities, may decrease the workload of existing community workers.

Changes in the number of referrals, demand for counselling, uptake of immunisation and presentation for growth monitoring services will be measured with routine trial monitoring forms. The value of the change in demand for these services will be calculated using process data on the average time spent on each activity, and publically available data on the salaries paid to community workers.

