### Aim and objectives

The aim of the CARING economic evaluation is to measure the cost-effectiveness of a community intervention that includes participatory learning and action with women's groups and home visits to improve the growth of children under 2. Activities to strengthen local VHSNCs will be undertaken in intervention and control arms.

The specific objectives of the economic evaluation are:
To measure the costs of setting up and implementing the community intervention to improve children's growth and the strengthening of VHSNCs.To estimate the costs to the health system, of (a) treatment for SAM provided at Malnutrition Treatment Centres (MTCs) or Nutritional Rehabilitation Centres (NRCs); (b) increased care seeking at Primary Health Centres for childhood illnesses, as a result of the programme.To measure the direct and indirect cost of the intervention to the health system, when existing community health workers may take on a greater workload resulting from the intervention.To measure the direct and indirect cost of the participation of community leaders or VHSNC members in participatory meetings or other activities related to the intervention.To calculate the household costs of care seeking related to undernutrition and any costs of changing feeding and caring behaviours, for example, the possible costs of buying additional/different foods.To estimate the incremental cost-effectiveness of the intervention combined with strengthening of VHSNCs, as compared with strengthening VHSNCs alone, where all new activities are delivered in addition to existing government programmes.

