### Study setting

As described fully in the trial protocol,^17^ the CARING trial takes place in West Singhbhum (Jharkhand state) and Kendujhar (Odisha state) districts in India. Odisha and Jharkhand are among the poorest states in India, with high rates of child mortality and undernutrition,^25^
^26^ and female literacy rates below 50%.^27^ In 2010, under-5 mortality was estimated 61 and 83 per 1000 live births in rural Jharkhand and Odisha, respectively.^28^
^29^ In Jharkhand over 50% of children are stunted, and in Odisha over 45% are stunted.^25^
^26^ The study districts are predominantly rural, with a combined total population of ∼3.3 million.^17^

Community-based health and nutrition services for mothers and children in the study villages are provided by three community workers: an Anganwadi worker (AWW), an Accredited Social Health Activist (ASHA) and an Auxiliary Nurse Midwife (ANM). AWWs provide supplementary nutrition to pregnant women, breastfeeding mothers and children aged 6 months to 6 years. ASHAs support community members in accessing essential healthcare services and promote institutional deliveries. ANMs provide services such as childhood immunisation and essential medicines. Community-based services are supplemented with care from primary care centres, MTCs that specialise in the treatment of SAM and hospitals.

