#### Identification, measurement and valuation of resource use

These analyses will measure the cost-effectiveness of the intervention from a societal perspective. This perspective is the most comprehensive, taking into account costs incurred by the programme, implementing agencies or donors, providers and households.^36^ This perspective determines the time horizon of any modelling, the choice of costs and outcomes to be included in the analysis, and the measurement and valuation of costs and consequences of the intervention.^37^
^38^ In this section, we will describe in detail the proposed methods for measuring and valuing programme costs, provider costs and household costs. Programme costs include those incurred by the implementing agencies, that is, University College London, the Public Health Foundation of India (PHFI) and Ekjut (http://www.ekjutindia.org), a civil society organisation leading the study. The provider or health system costs are those incurred by MTCs, Primary Health Centres, community workers and VHSNCs. The household or user costs include those incurred by mothers and their families. Table 1 shows the flow of cost data collection described further below.

**Table 1 BMJOPEN2016012046TB1:** Steps in cost data collection

Cost category or perspective	Type of costs	Description	Source	Sample size
Project/programme	Direct	Costs of implementing the intervention	Project accounts of implementing agencies	N/A
Provider/health system	Direct	Costs of referrals made to MTCs	Project records for number of referrals, MTC costing study for unit costs of services	All referrals made in intervention and control clusters
	Indirect	Opportunity cost of increase in workload of CHWs	Time use survey with CHWs	A purposive sample of CHWs in both arms will be selected for time use interviews
		Opportunity cost of time spent by VHSNC members in meetings	Project records	All meetings held and number of people attending the meetings will be recorded
Patients/households	Direct	Household expenditure on food	Household consumption survey	A random subsample of 300 households
		Cost of care seeking for mothers and children	3-month and 18-month follow-up surveys with mothers	All participants in the study
	Indirect	Opportunity cost of participation in groups and home visits	Household time use survey	A random subsample of 120 mothers, with children aged 13–18 months

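### Services from existing community workers are costed as labour only, so vaccine and supplementary-food costs have no place in the societal cost difference

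*Protocol article*

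**What the plan says.** The Community workers section names the services to be compared between arms: "Changes in the number of referrals, demand for counselling, uptake of immunisation and presentation for growth monitoring services". Routine trial monitoring forms supply the quantities. The value of any change is then to be "calculated using process data on the average time spent on each activity, and publically available data on the salaries paid to community workers".

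The Study setting section describes what these workers hand over. On food: "AWWs provide supplementary nutrition to pregnant women, breastfeeding mothers and children aged 6 months to 6 years". On vaccines and drugs: "ANMs provide services such as childhood immunisation and essential medicines".

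Three other places set the frame:
- Perspective, under Identification, measurement and valuation of resource use: "These analyses will measure the cost-effectiveness of the intervention from a societal perspective".
- Third objective, under Aim and objectives, for the case where existing community health workers take on more work: "To measure the direct and indirect cost of the intervention to the health system".
- Table 1, provider rows: the community-worker entry is "Opportunity cost of increase in workload of CHWs", placed under Indirect. The only provider row under Direct is referrals to malnutrition treatment centres (MTCs).

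**The concern.** A societal cost difference should contain every resource whose use differs between the arms, whoever pays for it. A vaccine dose or a food ration drawn from a government programme is such a resource. Under the stated rule, one more vaccinated child costs the worker's minutes and nothing else. One more child receiving the Anganwadi ration is not counted, because ration uptake is not among the tracked services.

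Supplementary food is a background service close to a growth outcome, and the intervention counsels mothers on feeding, so a difference in uptake between arms is plausible. If there is one, every cost-effectiveness ratio in the article has the wrong numerator. The plan also treats like items differently: under Programme-related costs, donated goods missing from the accounts are added at market value, but no such step is applied to government goods delivered by community workers.

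**Working it through.** The article states no figure on this point, so there is nothing to reproduce. The check traces each provider and household cost line to its quantity and its unit value.

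- **MTC care:** admissions by arm; average unit cost by step-down costing. Not limited to labour.
- **Primary Health Centre care:** change in demand by arm; published unit costs of treatment. Not limited to labour.
- **Community workers:** four tracked services; time multiplied by salary. Labour only.
- **Village committees:** meetings, duration and attendance; members' time at salary or salary equivalent. Time is the relevant resource here.
- **Households:** food spending, care-seeking costs and time use. Food spending is a household outlay and does not price a free government ration.

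Of the four tracked community services, immunisation is the one that plainly hands over a commodity. It has a quantity but no commodity price. Supplementary food has neither. The third objective covers direct and indirect cost, whereas Table 1 has no Direct row for community workers, so the two do not agree.

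The omitted term per child is

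omitted cost = (uptake in intervention arm − uptake in control arm) × (months eligible) × (commodity cost per month).

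Its sign follows the uptake difference. For rations to children only:

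- Months eligible: rations start at 6 months of age and follow-up ends at 18 months, so 18 − 6 = 12.
- Children per arm: n = 2520 in Trial design; an equal split is assumed, so 2520 / 2 = 1260.
- Uptake difference: not in the article; assumed range 5, 10 and 20 percentage points.

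Results:
- 5 points: 0.05 × 12 = 0.6 ration-months per child; × 1260 = 756 in the intervention arm.
- 10 points: 0.10 × 12 = 1.2 per child; × 1260 = 1512.
- 20 points: 0.20 × 12 = 2.4 per child; × 1260 = 3024.

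Each is multiplied by a unit price that the article does not give. A fall in uptake of the same size gives the same figures with the opposite sign. Rations to mothers and vaccine doses are not in this illustration.

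**The case against.** The strongest reply has four parts.

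1. The rule covers only four services, and three of them are mostly labour. Food is outside the list rather than valued at zero by the rule. Table 1 also plans a time use survey of community workers in both arms, which could capture Anganwadi time spent distributing food. This is right, and it narrows the gap to commodity prices and ration quantities. It does not close it.

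2. A difference between arms is not shown. The article describes counselling on feeding, infection control and care giving, and does not mention promotion of government rations. The activity described as addressing gaps in services is committee strengthening, which runs in both arms. It also says that the government scheme mainly serves children aged 3–6 years and that reforms reaching younger children are at an early stage. This stands against any claim about size, but the plan itself expects demand for community services to change and sets out to value that change.

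3. A journal article leaves detail to other documents. Here the article says that its purpose is a full account of the economic methods, and it states a specific valuation rule. Followed as written, the rule gives an incomplete cost.

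4. Stronger readings are tempting and do not hold. A reader might infer that all government services are costed as labour; MTC and Primary Health Centre care are not. A reader might infer that the intervention must look too cheap; the article allows that the new worker may reduce existing workers' load, so the direction is open. A reader might expect free rations to appear as a household food saving with no government cost against it; the article does not say whether the consumption survey records free rations. Whether a growth effect came from counselling or from extra food is a question about mechanism, not a costing error.

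**Conclusion.** The point holds for services delivered by Anganwadi workers, Accredited Social Health Activists and Auxiliary Nurse Midwives. Their valuation omits the vaccine cost of extra immunisation, and supplementary food has no quantity or price in any cost line. This conflicts with the societal perspective and with the third objective as set against Table 1.

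The error in incremental cost is zero only if uptake of these commodities is equal in the two arms (or differences happen to cancel). Its direction depends on the uptake difference, and its effect on the ratios cannot be judged, because the article gives no prices, uptake rates or total incremental cost. The ration-month figures rest on an assumed uptake difference and an equal split of the cohort; they show scale per child, not materiality. The change should be made because following the stated rule would misstate provider cost and the repair is small.

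**What to change.** 1. In the Community workers section, value each change in service use as worker time plus commodity cost at published government unit costs. Immunisation is the minimum, since its uptake is already tracked.
2. Compare receipt of supplementary food, for mother and child, between arms where existing surveys or Anganwadi records hold it. Where they do not, cover it by a stated range of uptake difference and unit cost in the sensitivity analyses already planned.
3. Count free rations once, at government cost, and keep them apart from household food spending.
4. Add a Direct row for community services to Table 1 so that it matches the third objective.

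Items 1, 3 and 4 need published unit costs and edits to the text and costing tool; item 1 needs no new fieldwork. Item 2 is cheap only where receipt is already recorded. With recruitment closed in February 2015 and the trial due to finish in 2016, some survey rounds may have passed; uptake taken from records is less exact and may be incomplete for them.

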#### VHSNCs

During the course of the intervention, several participatory meetings will be held with VHSNC members. The number of meetings, their duration and participation is being documented by the project. The opportunity cost of the time spent by the VHSNC members will be measured as a proportion of their salary where they are paid a salary—or as a salary equivalent, where they are working as volunteers.

### Household or user costs

CARING may influence household costs in a number of ways. Changes in the quantity, variety or quality of food fed to pregnant women and young children, may increase household expenditure on food. The intervention may also increase care seeking. The effect on health spending of this change may be positive or negative. Increases in care seeking from a very low base may increase total spending on care. Conversely, a shift from curative to preventive care seeking may decrease spending on care. Similarly, improved early child nutrition that averts severe malnutrition and related illnesses, may also reduce the need for care seeking. Finally, as the intervention seeks to change health and nutrition-related activities, it may also change the allocation of time to these activities. Participation in women's group meetings and in home visits will also have a direct time ‘cost’.

Changes in food expenditure are measured with a comprehensive household consumption and expenditure survey conducted on a random subsample of 300 households (150 per trial arm). The consumption and expenditure model is conducted twice for each participating household, with the two data collection points 1 year apart. This allows the measure of interest to be the change in expenditure over a 1-year period, with that change compared between intervention and control areas.

Changes in health spending are measured with a set of questions on care seeking collected from all the mothers recruited in the project. Care seeking data are also collected at two time points in the trial; first when the pregnant mother is recruited and again when the baby is 18-month old. In this instance, the measure of interest is not the change in spending over that time period, but a comparison of absolute levels of spending between intervention and control families with children of the same age.

Finally, the time cost of group participation, participating in the actions taken by the group, engaging with home visits or changing health, nutrition or stimulation behaviours will be measured using a time use survey to be conducted on a subsample of 120 women, equally distributed across the intervention and control arms.

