### Study population

The CARING trial area includes 120 geographic clusters of around 1000 population, typically a village and any nearby hamlets. These clusters were purposively selected based on their population size. The study participants are pregnant women identified in the third trimester of pregnancy and all children born to pregnant women recruited between 1 October 2013 and 10 February 2015. Mothers and their children are followed up for a period of 18 months after the birth of the child.

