### Trial design

In the CARING trial, a total of 120 purposively selected geographical clusters, with an estimated total population of 121 531, were randomised to the two trial arms. The 60 clusters in the intervention arm received home visits, participatory learning and action meetings and support to VHNSCs as described further below. The 60 clusters in the control arm received only the support to VHNSCs. Study participants are pregnant women identified in the third trimester of pregnancy and their children (n=2520). The randomisation, which took place in July 2013, was stratified by district and by number of hamlets per cluster. The trial is ongoing and is due to finish in 2016.

In the intervention clusters, a community intervention to improve children's growth involving home visits to all children under 2 and monthly participatory learning and action meetings with women's groups, combined with VHSNC strengthening activities, is being implemented. In the control clusters, only VHSNC strengthening is implemented. In the following section, we present a brief description of the intervention strategies. A full description of the intervention design within the CARING trial is described in detail elsewhere.^17^

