### Community intervention to improve children's growth

The community intervention involves a community-based worker (known as Suposhan Karyakarta or SPK) carrying out two main activities: (1) undertaking monthly home visits and (2) facilitating monthly women's group meetings. An SPK will visit all pregnant women at least once during their pregnancy, and all mothers of children under 2 on a monthly basis, to counsel mothers on appropriate feeding, infection control and care giving. She also facilitates a cycle of monthly women's groups, where the discussions will follow a participatory learning and action cycle focused on maternal health, child health and nutrition. A four phase ‘participatory learning and action cycle’, adapted from previous studies,^30^ will guide the groups to identify and prioritise maternal and child health and nutrition problems, decide on locally appropriate solutions, then implement and evaluate the solutions. These meetings primarily target pregnant and lactating mothers, mothers of children under 2 and adolescent girls. In home visits and women's group meetings, the SPK uses a problem-solving approach.

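### Food cost is measured as a between-arm difference in one-year change, which gives the cost difference the ICER needs only if the first survey is unaffected by the intervention, and the protocol does not secure that

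*Protocol article*

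**What the plan says.** The section on household or user costs describes a consumption and expenditure survey "conducted on a random subsample of 300 households (150 per trial arm"), "conducted twice for each participating household, with the two data collection points 1 year apart". The food-cost measure is then fixed as "the measure of interest to be the change in expenditure over a 1-year period, with that change compared between intervention and control areas". The first survey is not called a baseline, and its date relative to the start of the intervention is not given.

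The next paragraph of that section deals with care-seeking costs, also collected at two time points, and chooses differently: "the measure of interest is not the change in spending over that time period, but a comparison of absolute levels of spending".

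On timing, the trial design section states: "The randomisation, which took place in July 2013, was stratified by district". The study population section defines the children followed as "all children born to pregnant women recruited between 1 October 2013 and 10 February 2015". The description of the intervention adds: "An SPK will visit all pregnant women at least once during their pregnancy". The cost-effectiveness section builds each ICER on the difference in mean cost between the two arms.

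**The concern.** The ICER numerator is a difference in cost between arms. A difference in change is another quantity: it removes whatever arm difference exists at the first survey. If that difference is chance imbalance or stable household heterogeneity, removing it is harmless or useful. If it is already an effect of the intervention, a real cost is subtracted from the numerator.

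Three features make an early effect plausible. Participants were recruited after allocation. Contact with the new worker starts before birth. The article itself expects food changes for pregnant women as well as for young children. If food spending rises and part of the rise precedes the first survey, the societal cost is too low and the ICER too favourable. Extra food purchase is named in one of the specific objectives, and the results are meant to inform scale-up decisions.

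**Working it through.** **Inputs from the protocol article.** 300 households, 150 per arm; two surveys one year apart; randomisation in July 2013; recruitment from 1 October 2013 to 10 February 2015; at least one worker visit in pregnancy. No standard deviation (SD), within-household correlation, intracluster correlation or detectable difference is given for food spending, so there is no precision figure to reproduce. The 300 is simply 2 × 150.

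**Assumed.** Equal SD s at both surveys; within-household correlation r, shown over a range; illustrative effects in SD units.

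**What each analysis estimates**, with true arm differences d1 and d2 at the first and second survey:
- change contrast: d2 - d1
- second survey alone: d2
- ANCOVA (second survey adjusted for the first): d2 - r·d1
- mean of the two levels: (d1 + d2)/2

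| d1, d2 (SD) | Change | Second survey | ANCOVA, r = 0.5 | Mean of levels |
|---|---|---|---|---|
| 0, 0.30 | 0.30 | 0.30 | 0.30 | 0.15 |
| 0.15, 0.30 | 0.15 | 0.30 | 0.225 | 0.225 |
| 0.30, 0.30 | 0.00 | 0.30 | 0.15 | 0.30 |

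A simulation of 300 households in 120 clusters (assumed intracluster correlation 0.05, 2000 replicates) agreed with these values to within 0.005. If an effect fades, for example from 1 to 0.5, the change contrast is 0.5 - 1 = -0.5, so a real extra cost appears as a saving.

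No single analysis is right in both timing scenarios. With an unaffected first survey, the mean of levels dilutes the second-survey effect. With an affected one, both the change contrast and ANCOVA are biased for it.

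**Precision.** Variance of the arm contrast, as a multiple of 2s²/150 and before clustering: change 2(1 - r); second survey 1; ANCOVA 1 - r²; mean of levels (1 + r)/2. Since √(2/150) = 0.1155, the standard errors in SD units are:

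| r | Change | Second survey | ANCOVA | Mean of levels |
|---|---|---|---|---|
| 0.3 | 0.137 | 0.115 | 0.110 | 0.093 |
| 0.5 | 0.115 | 0.115 | 0.100 | 0.100 |
| 0.7 | 0.089 | 0.115 | 0.082 | 0.106 |

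- Change against ANCOVA: 2(1 - r)/(1 - r²) = 2/(1 + r), above 1 for every r below 1. This gives 1.54, 1.33 and 1.18 at r = 0.3, 0.5 and 0.7. At 80% power and two-sided 0.05, the detectable differences are 0.38 against 0.31 SD, 0.32 against 0.28, and 0.25 against 0.23.
- Change against second-survey levels: 2(1 - r) > 1 only if r < 0.5.
- Change against the mean of levels: 2(1 - r) > (1 + r)/2 only if r < 0.6.

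**The case against.** The strongest reply is that the bias depends on a date the article does not give. The article is condensed and refers to the trial protocol for detail, so the timing may be settled there. A first survey close to recruitment in the third trimester could not yet contain any effect of feeding the child about to be born, so a total loss is a limiting case. Differencing also removes stable differences between households, a recognised choice with 150 per arm. All of this stands, and it makes the point conditional. It does not remove it, because the measure is fixed in the text while the condition it needs is not stated.

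A reader might infer that the change score is less precise than any alternative. The documents do not support that: they give no correlation, and above r = 0.6 the change score is more precise than either level comparison. Only ANCOVA has lower variance at every r below 1, and it is a clean replacement only where the first survey is unaffected. Nor does the article say that the change will be analysed unadjusted. Adjusting it for first-survey spending gives the same arm estimate as ANCOVA and may be specified elsewhere.

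A reader might also take the level comparison for care-seeking as a contradiction. It is not one. That paragraph makes the choice deliberately and compares families with children of the same age. It places collection at recruitment in pregnancy and at 18 months, so a change would mix life stages.

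**Conclusion.** The point holds conditionally. The stated measure estimates d2 - d1 and equals the second-survey cost difference only when d1 = 0. Recruitment after randomisation and exposure from pregnancy make d1 ≠ 0 plausible but do not prove it. The loss is none if the first survey precedes exposure, half if half of the effect is present by then, and all of it if the effect is constant across both surveys. The direction, an ICER that is too favourable, assumes that food spending rises.

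Two stronger readings should be resisted. One is that the plan is known to lose the food cost: the first survey is not dated against exposure, so the size of any loss cannot be determined. The other is that food is the main household cost: the article also lists care-seeking and time costs and does not rank them. The precision figures rest on assumed correlations and equal SDs.

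**What to change.** State when the first consumption survey falls relative to the start of exposure, then tie the analysis to it.

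- **If it follows the start of exposure:** base the cost on the between-arm difference in expenditure levels at both surveys, allowing for clustering and accumulated over the exposure period. Keep the change contrast as a sensitivity analysis. The price is a wider interval than the change score gives if the within-household correlation exceeds about 0.6.
- **If it precedes exposure:** the change contrast is unbiased for the second-survey difference, but analyse second-survey expenditure adjusted for first-survey expenditure, allowing for clustering. This lowers the variance at any correlation below 1.

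Either route uses the same 300 households and the same two surveys. The cost is a sentence on timing, revised analysis wording and some analysis work.
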